**b. On and off-label uses of Gabapentinoids**

Licensed indications of gabapentinoids from across the world have since expanded to conditions including neuropathic pain, fibromyalgia, postherpetic neuralgia, restless legs syndrome, generalised anxiety disorder, menopausal symptoms and complications of multiple sclerosis.^13-16^ In addition to their licensed indications, off-label prescribing of gabapentinoids also accounted for a considerable proportion of their use.^17,18^ Given their effects on intracellular calcium levels, a considerable proportion of gabapentinoid prescriptions are for the treatment of mental health symptoms and diagnoses, such as insomnia and bipolar disorder, which, however, have limited evidence of efficacy to support their use.^2,19^

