**Study population**

All Individuals aged 18 or above who received at least one prescription for gabapentinoids (BNF chapter 4.8.1) and received at least one diagnosis of any of the outcomes of interest listed above between 1^st^ January, 2010 and 31^st^ December, 2020 in the CPRD, HES, and ONS Death Registration Data will be eligible for inclusion.

*Observation period*

The observation period will begin on 1^st^ January, 2010 or 18^th^ birthday of the individual or when the patient first join the GP practice (whichever was later) and end on 31^st^ December, 2020 or date of registered death or when the GP practice stops recording healthcare data for that patient (whichever was earlier).

*Exclusion criteria*

Individuals meeting any of the following criteria will be censored:

- Individuals who experienced any of the study outcomes before the observation period will be excluded.
- Patients who have a diagnosis of epilepsy.
- Patients with diagnosed cancer.
- Patients with missing information on date of birth and sex.

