**Exposures**

Prescriptions of gabapentin (Anatomical Therapeutic Chemical code N03AX12) or pregabalin (N03AX16) will be identified in CPRD. The exposed period is defined as the time receiving the medication, calculated with the prescription information in CPRD (daily dosages and quantity prescribed).

The index date is defined as the first date of prescription of gabapentinoid medication. We will calculate the length of exposure using information on prescription date and prescribed days in the database. Patients will contribute to consecutive exposure risk periods while they were continuously exposed to the drug.

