**Statistical Analysis**

Gabapentinoid usage is diverse with multiple indications. It can be prescribed for neuropathic pain, fibromyalgia, postherpetic neuralgia, restless legs syndrome, generalised anxiety disorder, menopausal symptoms, complications of multiple sclerosis, insomnia and bipolar disorder.^2,13-16,19^ There is no other way to estimate their effects for a particular group of patient without using a stratified analysis. SCCS is a method of estimation that focuses on individuals and does not necessitate separate control groups.^33^ As a result, it is considered self-controlled, effectively eliminating the influence of time-invariant factors and we should not include time-invariant factors into the SCCS analysis.

In our study, we will determine the duration of exposure during the study period and compute the incidence rates for the specific outcomes of interest within each exposure risk period. To assess the association between gabapentinoid use and the risk of these outcomes, we will employ conditional Poisson regression. Conditional Poisson regression analysis will enable us to calculate incidence rate ratios (IRRs) by comparing the periods of exposure to gabapentinoids with unexposed periods, adjusted for age in 1-year bands, seasonal effect, and other concurrent medications. Adjusted IRRs, along with their corresponding 95% confidence intervals (CIs), will be estimated for the overall exposure as well as for each predefined exposure risk period. All statistical analyses will be conducted with a significance level of 5%. The calculated IRRs will be stratified by age, sex, ethnicity, types of gabapentinoids, dosage levels and pre-existing comorbidities.

In additional analyses, the interaction between gabapentinoids and opioids or benzodiazepines by comparing the incidence of all-cause drug poisoning across combined exposure windows with periods unexposed to either medication will be examined. Gabapentin-only compared with pregabalin-only treatment periods among individuals who received both drugs during follow-up will also be evaluated.

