A series of sensitivity analyses will be performed, including a spline-based self-controlled case series analysis, exclusion of patients who died within 6 months of the event, starting follow-up from the first neuropathic or chronic pain diagnosis, restricting to individuals with at least two gabapentinoid prescriptions, varying the length of the pre-treatment period, adjusting only for age and season, extending treatment periods. Self-controlled case series extensions analyses will also be conducted.^34^ A negative control analysis will be performed to explore residual confounding. An additional case-case-time-control analysis^35^ is to validate the main findings, in which the 30 days before the event served as the hazard period and were compared with four randomly selected 30-day reference periods 61 to 180 days earlier, future cases occurring 180 to 360 days later were matched by age, sex, and ethnicity, and adjusted odds ratios (aORs) were estimated using conditional logistic regression. A two-sided significance level of 5% was used for all analyses.

For data analysis, we will utilise either the Statistical Analysis System (SAS) or R programming software.

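### The sensitivity analysis starting follow-up at the first pain diagnosis changes the population as well as the start date, so it needs a like-for-like comparator (minor; main IRR unaffected)

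*Protocol*

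**What the plan says.** The Study population section admits any adult "who received at least one prescription for gabapentinoids (BNF chapter 4.8.1") who also has a recorded outcome in 2010-2020; no indication is required. Under its Observation period paragraph, time starts at the latest of 1 January 2010, the 18th birthday and joining the practice. None of these depends on a diagnosis.

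The Statistical Analysis section lists, as one phrase in a series of sensitivity analyses, "starting follow-up from the first neuropathic or chronic pain diagnosis". It gives no purpose for this check and does not name the estimate it is to be compared with.

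The same section lists uses that are not in themselves pain diagnoses: "restless legs syndrome, generalised anxiety disorder, menopausal symptoms, complications of multiple sclerosis, insomnia and bipolar disorder". Section b of the background says that "a considerable proportion of gabapentinoid prescriptions are for the treatment of mental health symptoms and diagnoses, such as insomnia and bipolar disorder".

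Two further rules bear on the check. Under Exclusion criteria: "Individuals who experienced any of the study outcomes before the observation period will be excluded". Under Exposures: "The index date is defined as the first date of prescription of gabapentinoid medication".

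**The concern.** A user with no recorded pain diagnosis has no start date under this rule and can only drop out. The check therefore re-times follow-up and restricts the population in one step, while the natural comparator, the main IRR, comes from everyone. No planned analysis keeps the pain-diagnosed group with the original start, and that is the fit that would separate the two changes.

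The stake is interpretation. A self-controlled IRR pooled over groups with different true IRRs lies between them, so removing one group moves it even when the start date is irrelevant. The opposite can also happen: a real start-date effect can be offset by the population change and look like agreement. The protocol itself argues that effects in particular patient groups can be estimated only by stratifying, so it does not take a common effect for granted.

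There are two lesser issues. In users first diagnosed after starting treatment, the index date, the earliest treated time and the 90-day pre-exposure window fall before the new start. It is also unclear whether the prior-outcome exclusion is re-applied at that start.

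**Working it through.** The plan gives no figure for this check, so there is none to reproduce. The sample size of 484 does not enter it.

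**1. Population change alone**

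All inputs are assumed, because the documents give none:
- exposed share of observation time f = 0.30;
- share of cases without a pain diagnosis m = 10% to 40%;
- one true IRR in pain-diagnosed users and another in the rest;
- no effect of moving the start date.

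For a case in a group with a given IRR, P(event falls in exposed time) = f·IRR / (f·IRR + 1 − f). Mix the two groups with weights 1 − m and m to get P. The pooled IRR is then [P/(1 − P)] / [f/(1 − f)].

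*IRR 1.3 with a pain diagnosis, 2.0 without.*
- Pain-diagnosed: 0.39/1.09 = 0.3578. Others: 0.60/1.30 = 0.4615.
- m = 10%: P = 0.9 × 0.3578 + 0.1 × 0.4615 = 0.3682. The odds are 0.5827, and 0.5827/0.4286 = 1.36.
- m = 20%, 30%, 40%: 1.42, 1.49, 1.55.
- The check keeps only the first group and gives 1.30 every time.

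*IRR 1.5 with a pain diagnosis, 1.0 without.*
- Pain-diagnosed: 0.45/1.15 = 0.3913. Others: 0.30.
- m = 10%, 20%, 30%, 40%: main IRR 1.44, 1.39, 1.33, 1.28.
- The check gives 1.50, a shift in the other direction.
- At m = 30%, a real start-date effect that lowered the pain-diagnosed IRR from 1.50 to 1.33 would make the check match the main IRR exactly and go unseen.

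*Sensitivity to f.* In the first scenario with m = 40%, the main IRR is 1.57 at f = 0.10 and 1.54 at f = 0.50, against 1.55 at f = 0.30. The exposed share matters little.

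**2. Population change and moved start together**

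A second model used 200,000 cases, an 11-year window, varying treatment start and duration, and no confounding. It compared three fits: everyone with the original start, pain-diagnosed users with the original start, and pain-diagnosed users with the diagnosis start. All values are again assumed.

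| True IRR (pain / other) | No pain diagnosis | Diagnosed after starting | Everyone, original start | Pain-diagnosed, original start | Pain-diagnosed, diagnosis start |
|---|---|---|---|---|---|
| 1.2 / 2.0 | 10% | 20% | 1.27 | 1.20 | 1.20 |
| 1.2 / 2.0 | 30% | 20% | 1.42 | 1.20 | 1.20 |
| 1.2 / 2.0 | 50% | 20% | 1.58 | 1.20 | 1.20 |
| 1.5 / 1.5 | 30% | 20% | 1.50 | 1.50 | 1.50 |
| 1.5 / 1.5 | 30% | 50% | 1.50 | 1.50 | 1.50 |

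In the first three rows the middle fit already gives the check's answer, so the whole shift is population change. In the last two rows nothing moves, although only 48% and 38% of events remain.

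**3. Truncation alone**

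In the same model the true IRR was 1.5 in both groups, the rate was doubled in the first three months of treatment, and 30% had no pain diagnosis. The main IRR is 1.80. The check gives 1.80 if 20% are diagnosed after starting and 1.75 if 50% are. Losing early treated time has a small effect here.

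**4. Prior-outcome exclusion**

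Someone whose only event precedes the diagnosis drops out in any case, having no event in the shortened window. Re-applying the exclusion would also remove people with a further event after diagnosis. The protocol does not say whether it is re-applied.

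**The case against.** The strongest objection is that this is operational detail. The check is one phrase among several, the SAP is not shown, and the treatment of users with no diagnosis or a late one is commonly settled there. That stands for the handling rules: their absence from the protocol is not a finding. Nor is a changed population unusual in a sensitivity analysis. Requiring two prescriptions and excluding deaths within six months also change it.

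Part of the heterogeneity is addressed elsewhere. The Study design section plans a subgroup analysis in patients with mental illnesses, and the IRRs are to be stratified by pre-existing comorbidities. Both would help a reader judge a shift. Neither names pain diagnosis, and neither fits the pain-diagnosed group with the original start.

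A reader might infer stronger points that the documents do not support:
- *The check is meant to show that confounding has been removed.* No purpose is stated. The analysis assigned to residual confounding is the negative control.
- *Many users lack a pain diagnosis.* Section b speaks of prescriptions for mental health reasons, and the list in Statistical Analysis says only what the drugs can be used for. Someone treated for insomnia or anxiety may also have a pain code. The share is unknown.
- *Users diagnosed after starting are removed.* They lose time and events before the diagnosis but can still contribute later time.
- *Anyone poisoned before the diagnosis is barred by the exclusion criteria.* The exclusion is tied to the observation period, which is defined by date, age and registration. The sensitivity analysis speaks of follow-up.

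What survives is narrower: having fixed this anchor, the plan has no like-for-like comparator by which to read the result.

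**Conclusion.** The point holds as a minor one. The main IRR is unaffected. The check can include only pain-diagnosed users while the main IRR covers all indications, so a difference between them, or agreement, has no single meaning unless the effect is the same in both groups.

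Under the assumed IRRs of 1.3 and 2.0, 30% exposed time and 10-40% of cases without a pain diagnosis, the gap is 1.36-1.55 against 1.30. With 1.5 and 1.0 the direction reverses. With a constant IRR the gap is zero. The documents give neither the shares nor the IRRs, so these figures show what could happen and do not predict what will. Truncation in users diagnosed late is a lesser matter: 1.80 to 1.75 at most in the cases tried.

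**What to change.** In the sensitivity-analysis paragraph of Statistical Analysis:

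1. State that this check is restricted to users with a recorded neuropathic or chronic pain diagnosis.
2. In those same users, fit the main model with the original observation start as well as with the diagnosis start, and interpret the check by comparing those two IRRs.
3. State whether the prior-outcome exclusion is re-applied at the new start.
4. Report how many cases are lost for each reason: no diagnosis, a diagnosis after the first prescription, or an event before the diagnosis.

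The cost is one extra model fit and a few sentences, with no new data. The downside is that the check then speaks only to pain-diagnosed users, which is already true of the rule as written.

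### Case-case-time-control analysis: random 30-day reference windows in days 61–180 almost always overlap; name the four consecutive windows and use a robust variance

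*Protocol*

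**What the plan says.** The last part of the protocol's Statistical Analysis section adds a check on the main self-controlled case series (SCCS): "An additional case-case-time-control analysis", intended to validate the main findings. It fixes these elements:

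- Hazard window: "the 30 days before the event served as the hazard period".
- Reference windows: "four randomly selected 30-day reference periods 61 to 180 days earlier".
- Comparison group for exposure trend: "future cases occurring 180 to 360 days later were matched by age, sex, and ethnicity".
- Model: "adjusted odds ratios (aORs) were estimated using conditional logistic regression".
- Test level: "A two-sided significance level of 5% was used for all analyses".

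The number, length, location and manner of selection of the reference windows are therefore all stated. Nothing is said about overlap, and no variance other than the model's own is named.

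**The concern.** The stated elements do not fit together. Four windows of 30 days fill the stated range completely, so a random selection either has nothing to select or produces windows that share days. Shared days enter the conditional likelihood more than once, as if each window were a separate look at the person's usual exposure.

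Two things are at stake. The analysis uses less of the reference time than it could, so its odds ratio is noisier. Its model standard error is also too small, so the 5% test rejects too often. A check meant to confirm or question the SCCS result would then look more decisive than it is.

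**Working it through.** **1. Whole windows inside the range.** Days 61 to 180 inclusive: 180 − 61 + 1 = 120 = 4 × 30. A 30-day window has 120 − 30 + 1 = 91 possible start days, giving C(91,4) = 2,672,670 sets of four distinct starts. The number without overlap is C(120 − 120 + 4, 4) = 1, namely 61–90, 91–120, 121–150 and 151–180. Random draws cover a mean of 78 of the 120 days (5th to 95th percentile 54 to 99).

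**2. Range read as bounding the start days.** There are 120 starts and the windows reach back to day 209, a span of 149 days. There are C(120,4) = 8,214,570 sets, of which C(149 − 120 + 4, 4) = C(33,4) = 40,920 do not overlap. That is 0.5%, so 99.5% overlap.

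**3. Null simulation (OR = 1).** Inputs from the protocol: one 30-day hazard window, four 30-day reference windows, conditional logistic regression, two-sided 5%. The protocol gives no figures for time on and off drug; Exposures says only that "Patients will contribute to consecutive exposure risk periods while they were continuously exposed to the drug". The following are therefore assumptions: two-state daily exposure with the mean on/off spells shown, a window counted as exposed if any day is exposed, 1,500 cases and 500 replicates.

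A case with *m* of its five windows exposed (1 ≤ *m* ≤ 4) has model probability *p* = *m*θ/(*m*θ + 5 − *m*) that the hazard window is an exposed one, where θ is the odds ratio. Information is I = Σ*p*(1 − *p*), the model SE is 1/√I, and the robust SE is √Σ(*x* − *p*)²/I, where *x* is 1 if the hazard window is exposed and 0 if not.

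| Mean on/off days | SD of log OR, fixed | SD, random | Ratio | Model SE/SD, fixed | Model SE/SD, random | Type I, fixed | Type I, random |
|---|---|---|---|---|---|---|---|
| 5/60 | 0.0642 | 0.0820 | 1.28 | 0.92 | 0.78 | 6.2% | 12.4% |
| 28/180 | 0.0830 | 0.1038 | 1.25 | 0.87 | 0.76 | 10.8% | 13.8% |
| 28/60 | 0.0684 | 0.0849 | 1.24 | 0.91 | 0.80 | 7.0% | 11.4% |
| 90/180 | 0.0901 | 0.1140 | 1.27 | 0.82 | 0.71 | 10.8% | 17.0% |
| 365/365 | 0.1367 | 0.1733 | 1.27 | 0.77 | 0.66 | 14.2% | 20.6% |

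Further runs with other case numbers and spell lengths widen the ranges to 24–32% for the extra noise, 11–22% for type I error with random windows and 6–15% with fixed windows.

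Under the start-day reading the same run gives SDs 10–19% larger than fixed windows (0.1499/0.1367 = 1.10 to 0.0761/0.0642 = 1.19) and type I error of 11–16%.

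**4. Why fixed windows are not enough.** Adjacent windows from one person carry similar exposure even without shared days, and the model treats the five windows as exchangeable. Hence the ratios of 0.77–0.92 in the fixed column. The robust SE divided by the empirical SD is 0.94–1.02 with fixed windows (0.0606/0.0642 to 0.0917/0.0901) and 0.93–1.02 with random windows (0.0766/0.0820 to 0.0869/0.0849). In the further runs a robust variance brought type I error to about 3–6.5%.

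**5. True OR of 1.5 (log OR 0.405).** Mean estimates were 0.471 fixed against 0.565 random at 28/180, and 0.520 against 0.622 at 90/180. The excess over 0.405 is 0.066 against 0.160, and 0.115 against 0.217. At OR = 1 neither scheme shifted the estimate materially.

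**Limit of the check.** The figures are for the unadjusted case-crossover part. The matched future cases would presumably use the same windows; a null extension that included them showed the inflation carrying over.

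**The case against.** The best defence is that the protocol gives this analysis only part of a sentence. It never says that windows may overlap or are drawn independently, and a sampling grid or variance estimator is the kind of detail that a statistical analysis plan may supply. That is fair as regards the missing variance estimator taken alone. It does not rescue the window wording: the protocol itself fixes count, length, range and random selection, and following those words gives a worse analysis than dropping the word *randomly*.

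A reader might infer that the windows are bound to overlap. The text does not support that. If 61 to 180 bounds the start days, 40,920 non-overlapping sets exist, and a non-overlap rule would leave a real random choice. What stands is that unconstrained draws almost always overlap.

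A reader might also blame overlap for the whole understatement of the standard error. Step 4 shows otherwise: part of it comes from serially correlated exposure and remains with fixed windows.

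The magnitudes do rest on assumed exposure patterns, hence the ranges. The Feasibility count section projects 80,000 people with a suicide attempt and 106,000 with an unintentional overdose. If even a small fraction enter this analysis, the loss of precision would matter little. The type I error, however, does not shrink with sample size.

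**Conclusion.** The concern holds in a limited form. The stated range admits exactly one non-overlapping set of whole windows, or almost none by chance if it bounds the start days. Taken literally, with whole windows inside the range, random selection costs about 24–32% in the standard deviation of the log odds ratio. With ordinary model standard errors it also gives a type I error of about 11–22% at nominal 5%. Fixed windows restore the precision; a robust variance restores the standard error. The size depends on exposure persistence, which had to be assumed; the direction was the same in every pattern tried.

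Two inferences should be avoided. One is that only the error bars are affected: that is true only at OR = 1. At a true OR of 1.5 the estimate moved away from 1, more with random windows; fixed windows removed roughly half of the excess, not all of it. The other is that the study's main result is in doubt. This is an additional validation analysis, and the conditional Poisson SCCS does not use these windows. If the analysts already use the four consecutive windows, correcting the window wording changes no result.

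**What to change.** In the Statistical Analysis section, replace the random selection with named windows and state the variance, for example:

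> The hazard period will be compared with four consecutive 30-day reference periods, at days 61–90, 91–120, 121–150 and 151–180 before the event. Confidence intervals will use a robust or bootstrap variance clustered on the case (or on the matched set).

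Both parts are needed: the first for precision and reproducibility, the second for a valid standard error. Neither fully removes the bias seen away from OR = 1, so the result should be read as a check on direction and rough size.

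The cost is a sentence or two and a small amount of programming for the variance. No new data and no random seed are needed. Correct intervals will usually be wider than those from fixed windows with model standard errors: in the table's settings, from about 3% (0.0606/0.0591) to 33% (0.1385/0.1045).

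### The case-case-time-control check treats a person's five serially correlated exposure windows as exchangeable, so model-based confidence intervals for the aOR are too narrow; the protocol should name a person-level robust standard error

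*Protocol*

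**What the plan says.** The Protocol (Statistical Analysis, sensitivity analyses) adds a second case-only design to confirm the SCCS result: "An additional case-case-time-control analysis". Its parts are:

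- Hazard window: "the 30 days before the event served as the hazard period".
- Reference windows: "four randomly selected 30-day reference periods 61 to 180 days earlier".
- Comparator for exposure trend: "future cases occurring 180 to 360 days later were matched by age, sex, and ethnicity".
- Estimation: "adjusted odds ratios (aORs) were estimated using conditional logistic regression".
- Test level: "A two-sided significance level of 5% was used for all analyses".

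The section does not mention dependence between one person's windows and names no variance estimator. On how exposure runs over time, the Exposures section says: "Patients will contribute to consecutive exposure risk periods while they were continuously exposed to the drug".

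**The concern.** The natural reading is a matched set of five windows per person: one hazard window and four references. Conditional logistic regression on such a set assumes that, under the null and given how many of the five windows are exposed, each is equally likely to be an exposed one. The model-based SE rests on the same assumption.

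Two features of the plan break it. Exposure is persistent, so neighbouring windows resemble each other more than distant ones do. And the hazard window is always the latest of the five, separated from the references by a further 30 days. It therefore departs from the set average more often than an interchangeable window would. The score then varies more than the model information allows, and the interval comes out too short.

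Dependence that comes only from stable differences between people is conditioned out and does no harm. Serial dependence is not. Matching to future cases deals with exposure trend, but the future-case odds ratio comes from the same window layout and has the same understated variance.

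At stake is the value of the check. An analysis meant to corroborate the main result should not reject a true null well above its stated 5%.

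**Working it through.** The Protocol states no sample size, power or expected odds ratio for this analysis, so there is no figure to reproduce.

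**Inputs from the Protocol.** Hazard window: days 1-30 before the event. References: four 30-day windows in days 61-180. That span is 180 − 61 + 1 = 120 days, and 120/30 = 4, so non-overlapping windows fill it exactly. In months, the windows sit at lags 0, 2, 3, 4 and 5. Two-sided 5%. Illustrative effect: 1.5, the planning IRR in Sample size consideration.

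**Assumptions.** Month-to-month exposure autocorrelation ρ from 0 to 0.95, two-state Markov exposure and, for the table, exposure prevalence 0.3. The Protocol gives none of these.

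**Step 1: hand check.** Take the null, with at most one start or stop of treatment across the five windows. If m windows are exposed, an exposed hazard window has score 1 − m/5 and the set has information (m/5)(1 − m/5). For a start, the switch positions from oldest to latest give m = 4, 3, 2, 1. The last position counts twice because two monthly boundaries separate the hazard window from the nearest reference. A stop gives the same squares with opposite sign.

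- Sum of squared scores: 0.04 + 0.16 + 0.36 + 2 × 0.64 = 1.84
- Sum of information: 0.16 + 0.24 + 0.24 + 2 × 0.16 = 0.96
- True to model variance: 1.84/0.96 = 1.92; SE ratio √1.92 = 1.38
- Actual size: P(|Z| > 1.96/1.38) = about 15.7%

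**Step 2: exact enumeration** of the 2⁵ exposure patterns with four non-overlapping windows. Cases are weighted by the true odds ratio in the hazard window, and future cases by the same ratio at their own later event. Net aOR = case OR / future-case OR, here with the future event 9 months later, the midpoint of 180-360 days. At the null both odds ratios share the same SE ratio, so it carries over to the log aOR.

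| ρ | True/model SE (null) | False-positive rate | Within-case OR, true 1.5 | Net aOR, true 1.5 |
|---|---|---|---|---|
| 0 | 1.00 | 5.0% | 1.50 | 1.50 |
| 0.3 | 1.10 | 7.5% | 1.57 | 1.57 |
| 0.5 | 1.18 | 9.6% | 1.62 | 1.62 |
| 0.7 | 1.26 | 12.0% | 1.69 | 1.65 |
| 0.8 | 1.30 | 13.2% | 1.72 | 1.59 |
| 0.9 | 1.34 | 14.5% | 1.76 | 1.40 |
| 0.95 | 1.36 | 15.1% | 1.78 | 1.23 |

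The shortfall in the model SE is 1 − 1/1.10 = 9% at ρ = 0.3, rising to 1 − 1/1.36, about 27% before rounding the ratio, at ρ = 0.95. Nothing is wrong at ρ = 0, which confirms the mechanism.

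**Step 3: sensitivity to lag and trend.** With future events at 6 and 12 months, the net aOR for a true 1.5 is 1.48 and 1.65 at ρ = 0.8, and 1.29 and 1.49 at ρ = 0.9. With an exposure trend it ran from 1.43 to 1.60 and the SE ratio from 1.11 to 1.23. With a true ratio of 1 the net aOR stayed at 1.0.

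**Step 4: day-level simulation.** Null; 5,000 cases and 5,000 future cases; four fixed non-overlapping windows; 2,000 replicates per scenario. Assumed mean episodes were 30 to 730 days and mean gaps 180 to 730 days. The model-based test rejected about 8.5% to 16% of the time. With person-robust SEs on the same 1:4 model it rejected 4.5% to 5.4% of the time.

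**Step 5: would 1:1 pairs cure the bias?** Pooled hazard-reference pairs recover a within-case OR of 1.50 at every ρ under stationary exposure. After division by the future-case OR (9-month lag) they give 1.27 at ρ = 0.9 and 1.16 at 0.95. Both are further from 1.5 than the 1:4 values of 1.40 and 1.23.

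**The case against.** Three points can be made for leaving the text alone.

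*The variance estimator belongs in a SAP.* The Protocol does not say the SE is model-based, and a SAP that was not available here may specify a robust one. This has weight: if it does, the width problem is already solved. But the Protocol fixes the window layout, the model and the 5% level, and anyone following it with the usual output of that model gets intervals that are too short. The point concerns the stated method, not a missing detail.

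*The size is assumed.* True. The Protocol gives neither episode lengths nor autocorrelation. The direction is less open: the interval was too narrow in every scenario run with serial correlation.

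*It is one additional analysis.* Also true, and it limits the consequence.

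A reader might go further and infer that any non-null aOR from this analysis is inflated, so that it would always appear to strengthen the SCCS result. The Protocol does not support that. The reported aOR is adjusted by people who later have the same event. When exposure is highly persistent, their exposure at the index date already carries part of the effect, and dividing by their odds ratio pulls the net figure towards 1. The bias away from 1 belongs to the within-case component. For the same reason, replacing the 1:4 model with 1:1 pairs is no general remedy.

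**Conclusion.** The concern holds for the error bars. Under any serial persistence of exposure that was examined, the model-based SE for this analysis is too small, by about 9% to 27% for an assumed ρ of 0.3 to 0.95, and the nominal 5% test has a true size of about 7.5% to 15%. This does not depend on windows overlapping.

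For the point estimate a narrower statement holds. There is no bias when the true ratio is 1. Off the null, the within-case OR is exaggerated under stationary exposure, while the net aOR may err in either direction according to persistence, trend and where in the 180-360 day range the future event falls.

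The figures rest on a Markov exposure model and an autocorrelation the Protocol does not state. The SCCS conditional Poisson IRRs are untouched. The change is worth making because this check is offered as validation.

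**What to change.** In Statistical Analysis, add to the description of the case-case-time-control analysis that confidence intervals and tests for the aOR will use a person-clustered sandwich SE, or a person-level bootstrap, with all of a person's appearances as case or future case in one cluster.

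Pooled 1:1 hazard-reference pairs, or a Mantel-Haenszel estimate over the four windows, may be reported as a supplementary check on the within-case OR. They should not replace the 1:4 estimator as a cure for bias in the net aOR. The write-up should say that the net aOR can be biased in either direction when exposure is persistent.

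The cost is one sentence and a few lines of SAS or R code, with no new data. The downside is wider intervals: at the SE ratios above, about 10% to 36% wider than the model-based output. A robust SE corrects the width and the test size but leaves any off-null bias in the point estimate.
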